### Groups and interventions

2.2

Participants will be allocated to one of two non-randomized, parallel groups based on their acceptance to use the wearable device:
Intervention Group – AI-Based Remote Monitoring: Patients in this group will wear wearable devices continuously over a six-month period. The wearable device collects multimodal biometric data, including SpO₂, HRV, EDA, respiratory rate, skin temperature, pulse rate, and sleep metrics (actigraphy). These data are automatically transmitted to the SMART-CARE platform, where advanced AI algorithms analyse trends and detect early signs of clinical deterioration. In case of abnormal findings, the system generates alerts for the clinical team, which may initiate teleconsultations, therapy adjustments, or in-person evaluations to prevent acute decompensation.Control Group – Standard Clinical Follow-Up: Participants in the control group will receive standard CHF management in accordance with current European Society of Cardiology (ESC) guidelines. This includes outpatient visits every three months, ECG and echocardiographic assessments, and laboratory evaluations. No remote monitoring will be applied in this group. Clinical decisions, including medication adjustments, will be based on periodic clinical evaluations and patient-reported symptoms.

### Technological solution used for the AI-based remote monitoring group

2.3

The architecture is compliant with the General Data Protection Regulation (GDPR) and implements international interoperability standards (HL7/FHIR), thereby allowing integration with local electronic health records (EHRs) and hospital information systems. It is organized into layered components to guarantee scalability and flexibility:
An access layer providing secure authentication, authorization, and full audit trails;An application layer incorporating a patient dashboard for real-time visualization of biometric trends, a workflow engine for automated monitoring and alert-response processes, videoconferencing and chat modules to support synchronous and asynchronous communication, and questionnaire/PRO management tools;A service layer including a message broker for asynchronous communication, a complex event processing engine to transform raw IoT streams into clinically relevant events, and machine learning services for predictive analytics;A data layer responsible for the secure storage of structured, semi-structured, and unstructured data, ensuring persistence of time series, medical imaging, and laboratory information in compliance with international standards.On the patient side, the monitoring system relies on an integrated set of wearable and IoT devices. These include the EmbracePlus wearable (Empatica Inc.), selected for its CE-certification, multi-sensor capability, and validation in continuous physiological monitoring, as well as additional complementary devices such as blood pressure monitors, weight scales, glucometers, pulse oximeters, wearable movement sensors, and non-invasive hemodynamic monitoring systems. Together, these tools enable a comprehensive assessment of physiological parameters and patient status.

Data collected by the devices are transmitted via Bluetooth and encrypted cloud channels to the SMART-CARE platform, where they are processed by AI algorithms designed to detect abnormal trends and generate alerts for timely clinical action.

The artificial intelligence component of the SMART-CARE study will rely on an explainable, non-commercial predictive model based on Genetic Programming (GP), as recently described by Visco et al. (2024) (35). This algorithm employs a supervised learning framework in which clinical, biochemical, instrumental, and wearable-derived parameters are integrated through symbolic regression to generate transparent mathematical expressions. GP autonomously selects the most informative features and constructs human-interpretable predictive formulas, enabling clear visualization of variable contributions and overcoming the limitations of black-box AI models. This approach is particularly suitable for multimodal datasets collected in SMART-CARE, allowing real-time identification of early physiological deviations and supporting clinical explainability and bias assessment. The GP model will be adapted and retrained on the SMART-CARE cohort to evaluate its ability to predict early signs of worsening heart failure when combined with continuous wearable-derived physiological signals.

This integrated technological ecosystem ensures interoperability, scalability, and real-time responsiveness, enabling a truly AI-driven approach to remote monitoring and fostering the incorporation of digital health tools into routine clinical workflows (Figure 2).

**Figure 2 F2:**
[figure not shown]
Overview of the SMART-CARE telemedicine platform architecture. Wearable and multiparametric devices (EmbracePlus, Movesense/Polar H10, additional IoT sensors) transmit data via SDK/API REST to the telemedicine platform, which integrates with electronic health records, generates research datasets, and allows interoperability with external modules for advanced analytics.

This integrated technological ecosystem ensures interoperability, scalability, and real-time responsiveness, enabling a truly AI-driven approach to remote monitoring and fostering the incorporation of digital health tools into routine clinical workflows.

### Outcomes

2.4

Both groups will undergo assessments at baseline, 3 months, and 6 months, including evaluations of functional status, echocardiographic parameters, biochemical markers (e.g., BNP, NT-proBNP, renal function), and quality of life assessed using the Kansas City Cardiomyopathy Questionnaire (KCCQ) (36–39) (Table 2).

**Table 2 T2:** SMART-CARE outcome measures by timepoint.

Outcome type	Outcome measure	Domain	Baseline	3 months	6 months
Primary	Change in Hospital Admissions	Clinical Events			✔
Secondary	Change in Quality of Life (KCCQ Score)	Quality of Life	✔	✔	✔
Secondary	Adverse Effects of CHF Therapy	Safety			✔
Secondary	Change in BNP Levels	Biochemical	✔	✔	✔
Secondary	Change in NT-proBNP Levels	Biochemical	✔	✔	✔
Secondary	Change in Serum Creatinine	Biochemical	✔	✔	✔
Secondary	Change in eGFR	Biochemical	✔	✔	✔
Secondary	Change in Serum Sodium	Biochemical	✔	✔	✔
Secondary	Change in Serum Potassium	Biochemical	✔	✔	✔
Secondary	Change in Serum Chloride	Biochemical	✔	✔	✔
Secondary	Change in HRV	Functional (ECG)	✔	✔	✔
Secondary	Change in Respiratory Rate	Functional (ECG)	✔	✔	✔
Secondary	Change in LVEF	Echocardiographic	✔	✔	✔
Secondary	Change in E/A Ratio	Echocardiographic	✔	✔	✔
Secondary	Change in LV End-Diastolic Volume	Echocardiographic	✔	✔	✔
Secondary	Change in LV End-Systolic Volume	Echocardiographic	✔	✔	✔

CHF, chronic heart failure; KCCQ, Kansas City Cardiomyopathy Questionnaire; BNP, B-type Natriuretic Peptide; NT-proBNP, N-terminal pro-B-type Natriuretic Peptide; eGFR, estimated Glomerular Filtration Rate; HRV, Heart Rate Variability; ECG, Electrocardiogram; LVEF, Left Ventricular Ejection Fraction; E/A Ratio, Early to Late Ventricular Filling Velocity Ratio; LV, left ventricle.

The primary outcome of the SMART-CARE study is the relative reduction (≥20%) in hospital admissions, including emergency department visits and unplanned hospitalizations, over a six-month follow-up period in the intervention group compared to standard care (40). Hospitalization data will be collected prospectively and analysed for frequency, duration, and cause.

Secondary outcomes include:
Quality of Life (QoL): Measured using KCCQ at baseline, 3 months, and 6 months.Biochemical parameters: BNP, NT-proBNP, serum creatinine, eGFR, and serum electrolyte levels (sodium, potassium, chloride) at 3 and 6 months.Functional parameters: Variations in HRV and RR derived from wearable sensor data.Echocardiographic measures: LVEF, Early to Late Ventricular Filling Velocity Ratio (E/A ratio), and left ventricular end-diastolic and end-systolic volumes, measured at 3 and 6 months.Adverse events: Incidence of therapy-related complications such as hypotension and bradyarrhythmias.These outcomes will provide a comprehensive evaluation of the impact of AI-driven remote monitoring clinical status, functional performance, biomarker trends, and patient-reported outcomes in individuals with CHF. The measurements collected by the minimally invasive devices will be uploaded to the “Smartcare” platform and analyzed using machine learning (ML) techniques to develop multiparametric scores capable of identifying the specific trajectory of patients affected by HF.

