Optimized heart failure therapy for at least 1 month prior to enrolment	Terminal illness with limited life expectancy (e.g., metastatic cancer, end-stage lung disease)
Any LVEF phenotype (HFrEF, HFmrEF, HFpEF)	Pregnancy
≥1 hospitalization or outpatient visit with IV therapy for CHF in last 12 months	Dermatological conditions or allergies preventing prolonged use of the wearable device
Ability to provide informed consent or availability of a legally authorized representative	Cognitive or psychiatric disorders impairing adherence to study procedures

CHF, chronic heart failure; eGFR, estimated Glomerular Filtration Rate; HFmrEF, Heart Failure with mildly reduced Ejection Fraction; HFpEF: Heart Failure with preserved Ejection Fraction; HFrEF, Heart Failure with reduced Ejection Fraction; IV, intravenous; LVEF, left ventricular ejection fraction; NYHA, New York Heart Association; VAD, ventricular assist device.

All clinical, instrumental, and biochemical data will be recorded in anonymized case report forms and stored in a secure digital database. Biospecimens (blood and urine) will be collected and retained for secondary biomarker analysis. The study protocol adheres to the Declaration of Helsinki and Good Clinical Practice guidelines, and it was approved by the regional ethics committee (Comitato Etico Campania 2; Approval No. 185867). The trial is registered at ClinicalTrials.gov with the identifier NCT06909682.

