### Safety management and contingency planning

2.5

An additional strength of the SMART-CARE design lies in the structured approach to emergency management. The platform is not limited to early detection but also integrates a predefined pathway to ensure patient safety in the event of acute clinical deterioration. Alerts generated by abnormal biometric trends prompt immediate evaluation by the clinical team, who can escalate the response according to severity—ranging from direct patient contact or urgent teleconsultation to expedited in-person assessment or activation of local emergency medical services (EMS, 112/118 in Italy). This structured hospital–community network ensures rapid intervention and continuity of care, thereby minimizing the risk of adverse outcomes and reinforcing the overall safety and feasibility of AI-driven remote monitoring in real-world settings.

In addition, a technical contingency plan is in place: in case of device malfunction, connectivity issues, or platform failure, patients are promptly supported by remote technical assistance, with the possibility of temporary transition to standard in-person care to guarantee uninterrupted clinical follow-up. All participants undergo structured onboarding, including device training and safety instructions, and those with limited digital literacy are required to have caregiver support; continuous technical and clinical assistance is available throughout the study period. Furthermore, all clinical and biometric data are transmitted and stored in secure, encrypted repositories, ensuring data protection, traceability, and real-time safety oversight. This integrated safety and contingency framework is designed to minimize clinical risks, enable rapid response to emergencies, and maintain high standards of care within a remote monitoring setting (Figure 3).

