#### Sample size calculation

2.6.3

Based on the primary objective of the study, a sample size calculation was performed using G*Power software. The estimation assumes a 20% relative reduction in the rate of hospital admissions (including emergency department visits and hospitalizations) in the intervention group compared to the control group. Using a two-sided alpha of 0.05 and a statistical power (1–*β*) of 85%, the required sample size was calculated to be 186 participants. To account for a potential 10% dropout rate, the total planned enrollment is set at 205 patients with chronic HF. However, the study team elected to enroll 300 patients to further strengthen the statistical robustness of the analysis. This larger planned sample provides several advantages:
it compensates for potential attrition, incomplete adherence, or missing data;it increases the precision of effect estimates in a clinically heterogeneous HF population;it enhances the stability of exploratory subgroup analyses across LVEF phenotypes (HFrEF, HFmrEF, HFpEF);it improves the reliability and generalizability of machine-learning models derived from multimodal wearable data.Thus, while 205 participants represent the minimum requirement based on power analysis, the planned enrollment of 300 patients ensures greater analytical robustness and supports the broader aims of the SMART-CARE project.

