## Limitations

5

This study has several potential limitations that should be acknowledged. First, the non-randomized design may introduce selection bias, although the use of statistical adjustment methods (including multivariable regression and propensity score analyses) is expected to mitigate this risk. Second, the adoption of wearable devices may be influenced by a digital divide, with older or less digitally literate patients potentially underrepresented in the intervention group, which could limit the generalizability of the findings. Third, the reliance on continuous biometric monitoring and AI-driven alert generation raises the possibility of false positives, which may result in unnecessary clinical evaluations and potentially increase healthcare utilization. Conversely, false negatives cannot be excluded, with the risk of delayed detection of clinical deterioration. Finally, adherence to wearable use may vary over time, and incomplete data capture could affect the robustness of the analyses.

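### Three sections define the primary event differently, and an admission arranged after an alert, which only the device group can have, may go uncounted

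*Protocol article*

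**What the plan says.** The protocol article describes the primary event in three places.

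- **Outcomes (2.4):** "the relative reduction (≥20%) in hospital admissions, including emergency department visits and unplanned hospitalizations, over a six-month follow-up period", device group against standard care. Table 2 labels the same measure as a change in hospital admissions.
- **Sample size calculation (2.6.3):** the assumed 20% reduction is "in the rate of hospital admissions (including emergency department visits and hospitalizations) in the intervention group compared to the control group". The word *unplanned* is absent.
- **Primary endpoint analysis (2.6.1):** Kaplan–Meier curves, a log-rank test and a Cox model for the time to a first hospitalization. ED visits are not named.

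The two groups reach care differently. In the device group an alert goes to the clinical team, "which may initiate teleconsultations, therapy adjustments, or in-person evaluations to prevent acute decompensation" (Groups and interventions, 2.2). Section 2.5 describes an escalating response, "ranging from direct patient contact or urgent teleconsultation to expedited in-person assessment or activation of local emergency medical services". Controls have no remote monitoring: "Clinical decisions, including medication adjustments, will be based on periodic clinical evaluations and patient-reported symptoms".

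Table 1 requires at entry "≥1 hospitalization or outpatient visit with IV therapy for CHF in last 12 months". Neither Table 2 nor section 2.4 lists outpatient IV therapy as an outcome during follow-up.

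**The concern.** Whether an admission is planned or unplanned depends partly on how the patient came to the hospital. Alerts change that in one group only. A device patient called in by the team and then admitted could be recorded as a planned admission. A control with the same episode would more likely come through the ED, and that is counted under 2.4 whatever follows. Under 2.6.3 both would count. Under 2.6.1 the control's ED visit might not count unless it led to a ward stay.

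The classification of a similar episode can therefore depend on group, and on which section the person coding events follows. Propensity score matching cannot correct this, because the difference arises after baseline. The analysis of cause and duration in 2.4 describes only the events that were captured.

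**Working it through.** **1. The three definitions side by side**

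| Episode | 2.4 Outcomes | 2.6.3 Sample size | 2.6.1 Primary analysis |
|---|---|---|---|
| ED visit, no admission | counts | counts | not named |
| ED visit, then admission | counts | counts | counts |
| Admission arranged after an alert | unclear (is it unplanned?) | counts | counts as a hospitalization |
| Outpatient IV therapy for CHF | not named | not named | not named |

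Row three can arise only in the device group. Row four is accepted at entry but is in no listed outcome.

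**2. Size, under assumptions**

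The plan's only figure on this point is the 20% target. It gives no event rate and no frequency of arranged admissions, so r and f below are assumed.

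Take equal true event rates in both groups. Let r be the share of device-group events that go uncounted because they were arranged. Let f be the extra alert-generated ED visits, as a share of control events. Then

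apparent event ratio = (1 − r) + f.

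- r = 0.10, f = 0: 0.90, an apparent reduction of 10%
- r = 0.20, f = 0: 0.80, an apparent reduction of 20%, equal to the target
- r = 0.30, f = 0: 0.70, an apparent reduction of 30%
- r = 0.20, f = 0.20: 1.00, no apparent difference
- r = 0, f = 0.10: 1.10, an apparent excess of 10%

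The outcome is not restricted by cause. If only a share q of counted events are heart failure decompensations, and only those can be rerouted, the share of them that must be lost to produce 20% is 0.20/q: 25% at q = 0.8, 40% at q = 0.5, 50% at q = 0.4.

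**3. Effect on the planned test**

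With a constant hazard and losses unrelated to timing, losing a share r of events multiplies the device-group hazard by 1 − r. A loss of 20% thus acts as a hazard ratio of 0.80. Assume 150 patients per group and device-group risk of 0.8 times control risk p, so events = 300 × (p + 0.8p)/2. The Schoenfeld formula gives the chance of a significant apparent benefit as Φ(√events × |ln 0.80|/2 − 1.96):

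- p = 30%: 81 events, Φ(1.00 − 1.96) = 17%
- p = 50%: 135 events, Φ(1.30 − 1.96) = 25%

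The nominal rate in that direction is 2.5%. If the loss instead cut the proportion of patients with any event by 20%, a two-proportion comparison gives 21% and 41%.

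**4. Where double counting matters**

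If an ED visit and the resulting ward stay count as two and a direct admission as one, the ratio of counts is [2(1 − r) + r]/2 = 1 − r/2. This affects only the descriptive frequency summary in 2.4. In a time-to-first-event analysis each such episode gives one first event.

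**The case against.** The strongest reply is textual. Section 2.4 says *including*, not *only*, and no section excludes an admission arranged after an alert. An urgent admission from an expedited assessment is unplanned in ordinary usage. A reader might infer that the plan counts nothing except ED visits and unplanned stays, but the wording does not go that far. What stands is narrower: 2.4 singles out unplanned stays, 2.6.3 does not, and nothing says on which side an alert-arranged admission falls.

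Second, the Introduction states the objective as fewer hospitalizations. If early outpatient treatment replaces an admission, that admission was avoided and the outcome has done its job. A reader might infer that rerouting to outpatient care makes a positive result spurious. The documents do not support that, because this is partly the intended benefit. The argument does not cover an alert-arranged admission, which is still a hospital admission.

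Third, ED visits set off by false alarms are a real consequence of monitoring. The Limitations section concedes that false positives occur, "which may result in unnecessary clinical evaluations and potentially increase healthcare utilization". Counting these visits is correct for an outcome about hospital use. Removing them would take events from one group only, chosen by what happened afterwards.

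Fourth, KCCQ, natriuretic peptides and echocardiography are measured in both groups and help to interpret a fall in admissions. They do not recover uncounted events. Detailed coding rules may well sit in a fuller protocol, but the difference among the three sections is in the text shown.

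**Conclusion.** The point holds as an inconsistency in the event definition that carries a group-dependent risk of misclassification. It is not evidence that the trial will mislead. The three sections do not describe the same event, only the device group can have an alert-arranged admission, and outpatient IV therapy is recognised at entry but not in follow-up.

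The size is unknown. The relation that an apparent reduction is about r rests on equal true rates, no extra alert-generated visits and losses unrelated to timing. The documents give no value for r. A reader might infer from the 20% illustration that the target is likely to be met by reclassification alone, but nothing in the documents supports that. The distortion could also run the other way through alert-generated ED visits. Double counting of an ED visit and its admission is not a threat to the primary test.

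This is an inexpensive improvement, best made before events are coded, because route of entry is hard to reconstruct later.

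**What to change.** 1. In 2.4, 2.6.1 and 2.6.3, use one event definition. Count every non-elective admission in both groups whatever the route, explicitly including admissions arranged after an alert. Exclude only elective admissions already scheduled at baseline, a line drawn before monitoring can influence it.
2. Treat ED visits the same way in all three sections. Two of them already include such visits, so naming them in 2.6.1 is the smallest edit.
3. Add a supportive time-to-first-event outcome in both groups: hospital admission, ED visit or outpatient visit with IV therapy for CHF, to match the entry criterion in Table 1.
4. For the descriptive frequency summary only, count an ED visit and the admission it leads to as one event.

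Do not narrow the primary outcome to heart failure causes. That would be a new endpoint needing cause attribution in an unblinded study. Do not remove alert-triggered ED visits from the device group.

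The cost is one or two CRF fields (route of entry; IV therapy yes or no). Outpatient IV visits may be captured more completely in the monitored group, which would count against the device in the supportive outcome. The primary reduction may also look less favourable.

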#### Secondary endpoint analysis

2.6.2

Continuous variables will be presented as mean ± standard deviation (SD) for normally distributed data and as median and interquartile range (IQR) for non-normally distributed data. Categorical variables will be expressed as frequencies and percentages. The normality of distribution will be tested using the Shapiro–Wilk test. For normally distributed continuous variables, comparisons will be made using the paired t-test or one-way repeated measures ANOVA, depending on the situation. For non-normally distributed data, the Wilcoxon Signed-Rank test will be applied. Categorical variables will be compared using the Pearson chi-square test. Given the intrinsic differences in echocardiographic and clinical trajectories between HFrEF and HFpEF patients, all secondary endpoints (including echocardiographic parameters, biomarkers, and functional indices) will also undergo stratified analyses by LVEF phenotype. This approach is intended to avoid the dilution of clinically meaningful changes in subgroups with limited baseline variability, particularly among HFpEF patients. Subgroup analyses based on LVEF phenotype (HFrEF, HFmrEF, HFpEF) will be performed as exploratory analyses. The study is not powered to detect statistically significant differences between these subgroups; therefore, these analyses are intended to be descriptive and hypothesis-generating. To mitigate potential confounding when comparing phenotypes, LVEF category will be included as a covariate in multivariable models, and propensity score techniques will be applied when appropriate. Because echocardiographic parameters show markedly different baseline ranges and variability in HFrEF and HFpEF, echocardiographic secondary outcomes will also be interpreted within each LVEF phenotype. This approach is intended to avoid the dilution of true within-group changes in HFpEF patients, in whom structural parameters often fall within or near the normal range. A two-sided *p*-value < 0.05 will be considered statistically significant for all final analyses.

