## Expected results

3

We anticipate that AI-based remote monitoring with the integration of wearable devices will lead to a ≥20% reduction in hospital admissions over six months compared to standard care. Furthermore, we expect improvements in secondary outcomes, including enhanced quality of life, reduced therapy-related adverse events, and more favourable trends in biochemical and echocardiographic parameters. By enabling early detection of clinical deterioration and supporting timely intervention, the SMART-CARE system is expected to offer a more proactive, individualized, and data-driven approach to managing CHF. These findings may support the integration of wearable technologies and AI into routine clinical practice for heart failure patients, potentially reducing the burden on healthcare systems and improving long-term patient outcomes.

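### Change in serum potassium and in E/A ratio is tested only for a shift in location, so it cannot by itself show the favourable effect the article predicts; sodium and chloride share the problem to a lesser degree

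*Protocol article*

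**What the plan says.** Table 2 in section 2.4 (Outcomes) has 15 secondary rows. Four of them are signed changes in sodium, potassium, chloride and E/A ratio, worded for example as "Change in Serum Potassium" and "Change in E/A Ratio". The list below the table repeats the electrolytes under biochemical parameters ("serum electrolyte levels (sodium, potassium, chloride) at 3 and 6 months") and puts E/A under echocardiographic measures.

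Section 2.6.2 (Secondary endpoint analysis) gives one scheme for all continuous variables. On presentation: "Continuous variables will be presented as mean ± standard deviation (SD) for normally distributed data", with median and IQR otherwise. On testing of normally distributed variables: "comparisons will be made using the paired t-test or one-way repeated measures ANOVA", with the Wilcoxon signed-rank test otherwise. Testing is two-sided at 0.05, with added stratification by LVEF phenotype.

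The Results paragraph of the Abstract hypothesises a favourable effect on biochemical and echocardiographic parameters against standard care. Section 3 (Expected results) expects "more favourable trends in biochemical and echocardiographic parameters". Nowhere does the article give a direction, a reference range or a category for any of the four variables.

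**The concern.** A prediction that a parameter will move favourably needs a definition of better. For natriuretic peptides or LVEF, the direction supplies it. For potassium it does not, since both low and high values are harmful. For E/A it does not either: the ratio falls with impaired relaxation, rises back through the normal range as filling pressure increases, and is high in restrictive filling. These are general clinical facts that the article does not state.

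The matter is practical here. The intervention acts partly through therapy adjustments (section 2.2), and the Introduction gives diuretic dosage as its example. Electrolytes may therefore move either way in different patients. A null mean change could hide fewer out-of-range values. A significant shift could be described as benefit although more patients have left the range.

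Stratifying by LVEF phenotype does not resolve this. It separates neither low from high potassium nor one filling pattern from another.

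**Working it through.** The article gives no mean, SD, range or effect size for any electrolyte or for E/A, so there is no stated figure to reproduce. Its sample-size figures belong to the primary endpoint. Everything below rests on assumed inputs, including 150 patients per group: the article plans 300 in total and states no group sizes.

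**1. Potassium: the sign of the mean against the share out of range.** Assume a normal distribution with limits 3.5 and 5.5 mmol/L. The share out of range is Φ((3.5 - μ)/σ) + 1 - Φ((5.5 - μ)/σ).

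| μ | σ | z at 3.5 | z at 5.5 | Out of range | Of 150 |
|---|---|---|---|---|---|
| 4.5 | 0.6 | -1.67 | 1.67 | 9.6% | about 14 |
| 4.5 | 0.4 | -2.50 | 2.50 | 1.2% | about 2 |
| 4.8 | 0.6 | -2.17 | 1.17 | 13.7% | about 21 |
| 4.2 | 0.6 | -1.17 | 2.17 | 13.7% | about 21 |

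From the first row to the second, the share out of range falls from 9.6% to 1.2% with a mean change of zero. From the first row to the third or fourth, the mean moves by +0.3 or -0.3 and the share out of range rises to the same 13.7%. Opposite signs go with identical harm.

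**2. How far cancellation depends on the baseline mix.** Simulation of a potassium-like variable:
- range 3.5 to 5.0; patient groups centred at 3.2, 4.3 and 5.4; 40% of patients in the low and high groups together;
- the intervention moves those patients 0.5 towards the range;
- SD 0.15 around the centre at baseline and 0.35 at follow-up; 2,000 runs.

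The comparison is a two-sample t-test on change against a two-proportion test on the share in range. A between-group test is used because the prediction is against standard care. The expected mean difference is 0.5 × (share low - share high).

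| Low / high at baseline | Mean difference in change | t-test significant | Gain in share in range | Proportion test significant |
|---|---|---|---|---|
| 20% / 20% | 0.00 | 5.1% | 20.2 points | 98.7% |
| 30% / 10% | +0.10 | 52.4% | 20.6 points | 98.9% |
| 10% / 30% | -0.10 | 50.0% | 19.7 points | 97.4% |
| 40% / 0% | +0.20 | 98.6% | 20.7 points | 99.0% |
| 0% / 40% | -0.20 | 98.4% | 19.6 points | 97.5% |

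The benefit is about 20 points in every row. The mean difference is zero, positive or negative according to the mix alone. In the last two rows, where all abnormal values lie on one side, the mean change loses nothing and its sign can be read.

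**3. E/A.** A rise from 0.7 to 1.2 (+0.5) can be recovery to normal filling or progression to pseudonormal filling. A fall from 2.2 to 1.2 (-1.0) can be improvement and ends at the same value. If half the patients recover from 0.7 to 1.2 and half improve from 2.2 to 1.7, the mean change is 0.5 × 0.5 + 0.5 × (-0.5) = 0, although all have improved.

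**4. The rank test.** The signed-rank test also works on signed changes, so the route for non-normal data does not avoid the problem.

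**The case against.** The strongest reply is that reference ranges, shift tables and diastolic grading usually sit in an analysis plan or full protocol, and neither is shown. Naming a change in potassium as an outcome is not wrong in itself, and favourable is a word of the hypothesis rather than a success criterion. This stands in part: the absence of ranges alone would be no finding. But the article already fixes the outcome as signed change, the tests as tests of location, and the prediction as favourable for the classes that contain these variables. Taken together, they do not support one another for potassium and E/A.

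Three stronger readings are tempting, and the document does not support them:
- *The results will be read with the wrong sign.* The article assigns no sign to any of the four variables and tests two-sided. The sign is undefined, not wrong.
- *Benefit and harm will cancel.* This depends on the baseline mix, which is not given. The population is stable, on optimised therapy, and excludes eGFR below 30, so the 9.6% above is illustrative only.
- *Four of the 15 secondary outcomes are uninformative.* The case is firm for potassium and E/A. For sodium and chloride, change is interpretable if abnormal values are mostly on one side.

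It is also true that a narrowing of spread would show in the planned SD or IQR. That would make it visible descriptively, but the planned location tests would not test it.

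The adverse-event outcome does not clearly fill the gap. Its named examples are hypotension and bradyarrhythmias, though that list is not exhaustive.

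**Conclusion.** The point holds in limited form. For potassium and E/A, a shift in mean or signed rank cannot show a favourable effect, because the sign of the change does not identify benefit. Cancellation is possible but conditional: on the assumed inputs, the same gain of about 20 points is detected by the test on change in anything from 5% to 99% of runs, according to the baseline mix. Sodium and chloride are affected less.

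The conclusion rests on general clinical knowledge that potassium is harmful at both ends and that E/A is not monotone. The sizes rest on assumed distributions and 150 patients per group. The primary endpoint and the sample size are untouched. The change is worth making but is not critical.

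**What to change.** - **Electrolytes.** Keep the continuous change. Add a between-group comparison of the proportions below and above the laboratory reference range at 3 and 6 months, with low and high reported separately and adjusted for baseline status. Base any favourable statement on electrolytes on that comparison. Potassium matters most.
- **E/A ratio.** Report it descriptively and exclude it from the parameters on which a favourable effect is claimed. An ordered scale of impaired relaxation, normal or pseudonormal, and restrictive filling would not help. It merges normal with pseudonormal filling, so a move from 0.7 to 1.2 stays ambiguous, and separating the two would need diastolic measures that the article does not list.
- **Wording.** Limit the favourable prediction in the Abstract and section 3 to parameters with a stated direction, or to the range comparison above.

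The cost is wording in Table 2, section 2.6.2 and the two prediction statements; the electrolyte values are already collected. The drawback is that proportions are less precise than means when the shift is in one direction only, which is why the continuous change should stay.
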